### Statistical considerations

All statistical analyses will be performed by an independent statistician. The analyses will be performed on an intention to treat assumption, defined as all intentionally randomized patients, by randomization treatment. A detailed statistical analysis plan will be completed before the end of the study. In brief, continuous variables will be tested for normal distribution with the Kolmogorov–Smirnov test and with a visual estimate of *Q*–*Q* plot. Normally distributed variables will be presented as mean ± SD and compared by t-test and one-way ANOVA. Otherwise, median [inter-quartile range], Mann–Whitney *U* and Kruskal–Wallis tests will be used. Categorical variables will be summarized in terms of absolute and relative frequencies (percentages) and compared using the *χ*^2^ test. Statistical significance will be set at *α* = 0.05 level. Formal type-I error control will be ensured for the primary and the key secondary endpoint by a sequential procedure where significance for the key secondary endpoint is accepted only if the primary endpoint is positive. Kaplan–Meier curves will be plotted to describe freedom from adverse events, and difference between groups will be tested with the log-rank test. When appropriate, 95% CI will be calculated.

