### Study endpoints

The primary endpoint is the one-year occurrence of CV death or hospital readmission for CV causes (Table 2). In case of repeated adverse events, the first that occurred will be the one considered. A detailed list of secondary endpoints is reported in Table 2. Being the study population based on older MI patients for whom also non-CV outcomes have a great relevance, careful attention will be deserved in the collection of all serious adverse events, including all-cause death and all-cause readmissions to hospital (Table 2). Follow-up will continue until 3 years after the randomization (Table 2). A committee consisting of clinicians who are blinded to treatment allocation (Clinical Event Committee) will review and adjudicate all adverse events based on the source documents.

**Table 2 Tab2:** Study endpoints

	Timing	Endpoint
Primary	One-year	Cardiovascular death or hospital readmission for cardiovascular cause
Secondary	One-year	All-cause death
		Cardiovascular death
		Hospital readmission for cardiovascular cause
		Myocardial infarction
		Cerebrovascular accident
		Hospital readmission for any cause
		Quality of life (EQ-5D)
	Three-year	Cardiovascular death or hospital readmission for cardiovascular cause
		All-cause death
		Cardiovascular death
		Hospital readmission for cardiovascular cause
		Myocardial infarction
		Cerebrovascular accident
		Hospital readmission for any cause
		Quality of life (EQ-5D)

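### Kaplan–Meier is the only time-to-event estimator named, although deaths compete with every event endpoint except all-cause death, so reported absolute risks would run high, mainly at three years

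*Protocol article*

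**What the plan says.** Under Statistical considerations, the protocol article gives one sentence on event-time methods: "Kaplan–Meier curves will be plotted to describe freedom from adverse events", and the "difference between groups will be tested with the log-rank test". The same section summarises categorical variables as counts and percentages compared by a chi-square test. It is written as a short account, and "A detailed statistical analysis plan will be completed before the end of the study".

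Under Study endpoints, "The primary endpoint is the one-year occurrence of CV death or hospital readmission for CV causes", counting the first event. Table 2 lists seven event endpoints, each at one and three years: the composite, all-cause death, CV death, CV readmission, MI, cerebrovascular accident, and readmission for any cause. "Follow-up will continue until 3 years after the randomization". The section stresses outcomes outside the CV endpoints ("Being the study population based on older MI patients for whom also non-CV outcomes have a great relevance") and promises "collection of all serious adverse events, including all-cause death and all-cause readmissions to hospital", with blinded adjudication of all adverse events.

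**The concern.** A patient who dies of a non-CV cause can never go on to have the primary event. A patient who dies of any cause can never later be readmitted or have an MI or cerebrovascular accident. Kaplan–Meier with censoring at such a death treats the patient as someone who might still have the event, so one minus Kaplan–Meier exceeds the proportion of patients who actually have it. The article states the primary endpoint as an occurrence and the design rates as absolute risks (25% and 15%), and under competing deaths the quantity of that kind is the cumulative incidence. Only all-cause death is free of the problem. Patients are 65 or older, have had an MI and have reduced physical performance, so deaths outside the endpoint will occur, and more of them over three years than over one.

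At stake are the absolute risks, and any risk differences, that readers take from the curves.

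**Working it through.** **Inputs from the protocol article.** One-year primary event rates of 25% (control) and 15% (intervention), from Determination of sample size; 25% × (1 − 0.40) = 15%, so the two agree. Endpoints and horizons are from Table 2.

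**Assumptions.** The article gives neither a non-CV death rate nor a three-year event rate, so there is no stated figure for this bias to reproduce. I took non-CV death of 1–8% a year, constant hazards over three years, and censoring at a competing death (the usual handling, which the article does not spell out).

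**Formulas.** With event hazard λ and competing-death hazard μ = −ln(1 − annual death risk):
- one minus Kaplan–Meier = 1 − exp(−λt)
- cumulative incidence = λ/(λ + μ) × [1 − exp(−(λ + μ)t)]

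λ is set so that the one-year cumulative incidence equals 25% or 15%.

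**Worked case: control arm, 5% a year.** μ = −ln(0.95) = 0.0513 and λ = 0.2959.
- One year: 1 − exp(−0.2959) = 25.6%, against 25.0%.
- Three years: 1 − exp(−0.8877) = 58.8%. Cumulative incidence is 0.2959/0.3472 × [1 − exp(−1.0416)] = 55.2%. The excess is 3.7 points.

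**Excess of one minus Kaplan–Meier for the primary composite, in percentage points:**

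| Assumed non-CV death per year | Control, 1 y | Control, 3 y | Intervention, 1 y | Intervention, 3 y |
|---|---|---|---|---|
| 1% | 0.12 | 0.74 | 0.07 | 0.53 |
| 3% | 0.36 | 2.22 | 0.22 | 1.59 |
| 5% | 0.61 | 3.69 | 0.38 | 2.65 |
| 8% | 1.00 | 5.88 | 0.62 | 4.23 |

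**Between-arm difference.** Here λ is set the other way, so that one minus Kaplan–Meier equals 25% and 15% at one year (λ = −ln 0.75 and −ln 0.85). The Kaplan–Meier difference is 10.0 points at one year, against a cumulative-incidence difference of 9.95 (1% a year) to 9.63 (8% a year). At three years it is 19.2 against 19.0 to 17.6.

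**Set against sampling error.** With 152 and 304 patients, the one-year 95% half-width is 1.96 × √(0.25 × 0.75/152 + 0.15 × 0.85/304) = 1.96 × 0.0407, or about 8 points. The one-year shift of at most 0.4 points is small beside that.

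**A readmission endpoint, with all deaths competing.** Assuming a one-year Kaplan–Meier risk of 20% and all-cause death of 3–10% a year, the excess is 0.3–1.0 points at one year and 1.9–6.2 at three years. For a rarer event (assumed 5% at one year) it is 0.1–0.3 and 0.6–2.0 points.

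**The case against.** The strongest reply is that this is a condensed article with a detailed analysis plan to follow, and that nothing in it rules out a competing-risk analysis. That is fair, and if the analysis plan already provides one, the point is settled. But the article is not merely silent. It names an estimator and applies it to adverse events generally, and that estimator suits one event endpoint in seven.

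A reader might go further and infer that Kaplan–Meier is the only route to event risk. The text does not support that. Percentages with a chi-square test are also named, and with complete follow-up the number of events over the number randomised keeps competing deaths in the denominator and avoids this bias. They are only a partial answer: the article plans for 5% loss, and crude percentages do not handle censoring, which matters more over three years.

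A reader might also infer that the planned comparison is invalid. It is not: the log-rank remains a valid test of the cause-specific hazard. Nor does the article say that risk differences or numbers needed to treat will be read off the curves. The curves are there to describe freedom from events, so the bias arises when they are read as occurrence.

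Finally, the excess has the same sign in both arms and partly cancels in the contrast, and all-cause death and any-cause readmission are themselves secondary endpoints. Both points stand, and they limit the size of the problem.

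**Conclusion.** The point holds as one about describing absolute risk. Followed as written, with the usual censoring, the Kaplan–Meier sentence overstates occurrence for six of the seven event endpoints. The overstatement is minor for the one-year primary endpoint, at most about 1.0 point in an arm even at 8% a year non-CV death. In points it is roughly six to seven times larger at three years, and it can be larger again for readmission, where every death competes.

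The direction and the growth with time do not depend on the exact rates chosen. The sizes do: they rest on assumed death rates and on extending a constant one-year hazard to three years, neither of which the article supplies. It would be wrong to conclude that the primary result is at risk. The log-rank test, the sample size and the primary conclusion are unaffected by this point.

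**What to change.** In the analysis plan, for every event endpoint that does not count all deaths, and chiefly at three years, replace the Kaplan–Meier curves with Aalen–Johansen cumulative incidence curves. Treat as competing events non-CV death for the primary composite and for CV death, and any death for readmission, MI and cerebrovascular accident. Report risk differences with 95% CIs from these curves. Keep Kaplan–Meier for all-cause death, and keep the log-rank, labelled as a test of the cause-specific hazard.

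The cost is slightly more analysis work and slightly lower reported event risks. All deaths are already collected and adverse events adjudicated, so no new data are needed. An added composite endpoint or a different test is not needed to settle this point.

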### Screening, inclusion visit and randomization

All patients aged ≥ 65 years old admitted to hospital for MI and undergoing treatment of any coronary lesion considered suitable for revascularization will be provided information about the study protocol, aims, risks and benefits. MI diagnosis will be based on symptoms, electrocardiographic changes and rise and fall in cardiac biomarker (cardiac troponin), in agreement with current guidelines [15]. If the patient accepts to take part in the study and signs the informed consent, a study doctor will assess the SPPB. A brief description and interpretation of the SPPB test is reported in Fig. 2. Patients with an SPPB score of < 4 or > 9 will be excluded. Patients with an SPPB score of 4–9 are included in the run-in phase, and the study brochure will be provided. In the brochure, patients can find general recommendations about a heart-healthy lifestyle. One month after hospital discharge, during the inclusion visit (T1), the SPPB is re-evaluated and if the score is confirmed between four and nine, patients are randomized to multi-domain lifestyle intervention (intervention group) or the standard of care (control group) with a 2:1 allocation. Randomization is stratified by sex (male vs. female), SPPB value (4–6 vs. 7–9), clinical presentation (ST-segment elevation vs. no ST-segment elevation MI) and center. The key patient characteristics (i.e., inclusion/exclusion criteria, demographics, medical history, CV procedures, exams and treatments, laboratory test results) are recorded on the electronic Case Report Forms (eCRF, https://redcap.ospfe.it/).

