### Determination of sample size

Based on previous studies [13, 14, 18, 19], we may suppose a one-year primary outcome rate of about 25%. Previous studies showed a benefit from physical intervention ranging from 35 to 50%. Although the data should be considered with caution, we may suppose a reduction in the primary outcome of 40% (expected rate in the intervention arm 15%). Thus, based on alpha = 0.05 and beta = 80%, a total sample size of 435 patients is required. Estimating a possible loss of patients of 5% (*n* = 21), the final study population should be at least 456 patients, 152 in the control group and 304 in the intervention group.

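### Randomization is stratified on four factors, but the log-rank test named for event-free survival does not mention them; run plain, it would be valid but mildly conservative (minor)

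*Protocol article*

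**What the plan says.** Under Screening, inclusion visit and randomization, the article states: "Randomization is stratified by sex (male vs. female), SPPB value (4–6 vs. 7–9), clinical presentation", and adds centre as the fourth factor. Patients are allocated to the intervention "or the standard of care (control group) with a 2:1 allocation".

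Under Statistical considerations, Kaplan–Meier curves describe freedom from adverse events, and the "difference between groups will be tested with the log-rank test". The sentence says neither stratified nor unstratified. No regression model, adjustment or stratification factor is mentioned in the analysis text. The same section states: "A detailed statistical analysis plan will be completed before the end of the study", and presents what follows as a summary.

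Under Beyond the HULK study, the article reports that earlier studies linked SPPB to mortality. It gives no hazard ratio for SPPB or for any other stratification factor.

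**The concern.** Stratified randomization removes chance imbalance between the arms on the stratification factors. A plain log-rank computes its variance as if that imbalance could still occur. If the factors predict outcome, the variance is overstated, the test rejects too seldom under the null, and some power is lost. SPPB is both the eligibility gate and a stratification factor, and the protocol itself treats it as prognostic.

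At stake is a little efficiency and an analysis that matches the design. A positive result from a plain log-rank would still stand.

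**Working it through.** **Inputs from the article.** One-year event rates of 25% (control) and 15% (intervention), 2:1 allocation, alpha 0.05, power 80% (written as beta), 435 patients before loss and 456 after (152 + 304).

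**The plan's own figure.** The article says "based on alpha = 0.05 and beta = 80%, a total sample size of 435 patients is required". For two proportions with pooled variance and 2:1 allocation, the control-arm size is

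n = [z_α·√(1.5·p̄(1−p̄)) + z_β·√(p₁(1−p₁) + p₂(1−p₂)/2)]² / (p₁−p₂)²

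with p̄ = (0.25 + 2×0.15)/3 = 0.1833. The two roots are √(1.5×0.1497) = 0.4739 and √(0.1875 + 0.06375) = 0.5012.

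- One-sided 0.05: (1.645×0.4739 + 0.842×0.5012)²/0.01 ≈ 144.3, so 145 + 290 = 435. This matches.
- Two-sided 0.05: (1.960×0.4739 + 0.842×0.5012)²/0.01 ≈ 182.4, so 183 + 366 = 549.

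At two-sided 0.05, 435 patients give 70.9% power and 456 give 72.8%. These are the reference values for the simulations.

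**The two tests.** With one event at a time, r₁ intervention patients among r at risk, and each event scored 1 if it falls in the intervention arm and 0 otherwise:

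- Plain: Z = Σ(O − r₁/r) / √Σ[(r₁/r)(1 − r₁/r)], over all events pooled.
- Stratified: the same numerator and variance terms, computed within each stratum and then summed over strata.

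**Simulations** (two-sided 0.05). Stratum effects are assumptions, because the article gives none.

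- Set A: 456 patients, exponential event times, blocks of 3 within eight cells, marginal risks fixed at 25% and 15%, 3,000 runs.
- Set B: 435 patients, blocks of 3 within 40 cells (eight clinical cells × five assumed centres), 30% female, 35% SPPB 4–6, 45% STEMI, 4,000 runs. The within-stratum hazard ratio is ln 0.85/ln 0.75 = 0.565. Hazard ratios for sex/SPPB/STEMI and the centre log-hazard SD are: moderate 1.3/1.8/0.8, 0.2; strong 1.5/2.5/0.67, 0.4; very strong 2/4/0.5, 0.6.
- Set C: 456 patients, 25% against 15%, a further run with no, moderate and strong assumed effects.

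| Set | Stratum effects | Power, plain | Power, eight cells | Gain (points) | Type I, plain | Type I, eight cells |
|---|---|---|---|---|---|---|
| A | none | 72.9% | 73.2% | 0.3 | – | – |
| A | HR 2.0/1.3/1.3 | 74.3% | 75.4% | 1.1 | 4.2% | 5.0% |
| A | HR 3.0/1.5/1.5 | 75.2% | 77.6% | 2.4 | 3.7% | 4.5% |
| B | none | 72.1% | 71.8% | −0.3 | 5.3% | 5.5% |
| B | moderate | 72.5% | 72.8% | 0.3 | 4.9% | 5.0% |
| B | strong | 69.5% | 71.8% | 2.3 | 4.2% | 4.8% |
| B | very strong | 64.5% | 69.6% | 5.1 | 2.9% | 4.2% |
| C | none | 73.3% | 73.4% | 0.1 | – | – |
| C | moderate | 72.9% | 74.3% | 1.4 | – | – |
| C | strong | 74.2% | 76.4% | 2.2 | – | – |

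The Monte Carlo standard error in set B is about 0.7 points for power and 0.35 for type I error. Set C also showed no type I inflation of the plain test. Compare tests within a row only. Set B holds the within-stratum hazard ratio fixed, so the marginal effect shrinks as the strata become more prognostic, whereas set A holds the marginal risks fixed.

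**Why not cross with centre.** Expected events at 456 patients are 152×0.25 + 304×0.15 = 38 + 45.6 = 83.6. That is about 10 per cell over eight cells, but about 2 per cell over 40. In set B, stratifying on all 40 cells gave power of 71.3%, 71.3%, 71.2% and 70.5% (none to very strong). With moderate effects this is about 1 point below the plain test (72.5%). It beats eight cells only in the very strong case.

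**The case against.** The strongest objection is that the point rests on silence. The section is a summary, it defers to an analysis plan, and a stratified log-rank is still a log-rank test. How strata enter the analysis is commonly settled in that plan. This objection largely stands: a reader might infer that the trial has chosen to ignore its strata, and the article does not say so. What survives is that it names one test without qualification, that a reader would ordinarily take this as the plain version, and that nothing in the analysis text points to the strata.

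The objection that the gain is small also stands. It is within simulation noise in the weaker scenarios, and the assumed effects are not taken from the documents. The SPPB link the article cites concerns mortality, while the primary endpoint also counts cardiovascular readmission.

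Three further inferences are tempting and unsupported:

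- *That a chi-square test on the primary endpoint also ignores the strata.* The sentence reads "Categorical variables will be summarized in terms of absolute and relative frequencies (percentages) and compared using the" chi-square test. It covers categorical variables in general and is not assigned to the primary endpoint.
- *That error rates are distorted in a harmful direction.* The plain test's type I error was at or below nominal within simulation noise, falling to 2.9% at the extreme.
- *That stratifying would repair the sample size.* The gap from 72.8% to 80% at two-sided 0.05 is 7.2 points. It arises because 435 reproduces only with an undeclared one-sided alpha. That is a separate matter, and a gain of 0 to 2 points does not close it.

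**Conclusion.** The point holds as a minor one. The randomization uses four stratification factors, and the one test named for event-free survival mentions none of them. If that test is run plain, the result is valid and mildly conservative. It costs roughly 0 to 2 points of power under moderate to strong prognostic effects, about 5 under very strong ones (SPPB hazard ratio of 4), and nothing if the strata are not prognostic.

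These sizes rest on assumed stratum hazard ratios and, in set B, on assumed stratum frequencies and five centres. The direction follows from the design and does not depend on those values beyond the strata being prognostic. If the analysis plan already specifies a stratified test, there is nothing to change.

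**What to change.** State in the statistical analysis plan, before analysis:

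- The primary log-rank test is stratified by SPPB band (4–6, 7–9), sex and MI presentation (ST-elevation or not), giving eight cells.
- The cells are not crossed with centre, because that leaves too few events per cell; give this reason.
- The treatment effect is a Cox hazard ratio with 95% CI using the same three factors, so that estimate and test correspond.
- The plain log-rank is a sensitivity analysis.

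The cost is one paragraph. The factors are already recorded for randomization, so no new data are needed. Where the strata are not prognostic, the eight-cell test costs essentially nothing (72.1% against 71.8% in set B, within noise).

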## Introduction

Secondary prevention after myocardial infarction (MI) requires an integrated approach combining drugs (antithrombotic, anti-remodeling and lipid-lowering agents, beta-blockers), diet, smoking cessation, and measures to actively promote physical activity (home-based and/or supervised exercise intervention and/or cardiac rehabilitation program based on patient and acute event characteristics) [1]. The aging of the population, with the consequent increase in the mean age of patients admitted to hospital for MI, further stresses the importance of multi-domain cardiovascular (CV) secondary prevention. Older MI patients show several comorbidities and unrecognized but prognostically significant risk factors, such as low physical performance [2]. Older adults are the least fit and active group, and cardiovascular diseases accelerate physical deconditioning [3]. Low physical activity level is independently related to adverse events in patients with ischemic heart disease [4]. In addition, any hospital readmission further reduces the physical performance with potential prognostic worsening in terms of death [5]. Even though a multi-domain approach can be challenging in a specific subset of older patients, its value is undeniable, as shown by the FINGER (Finnish Geriatric Intervention Study to Prevent Cognitive Impairment and Disability) trial [6].

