### Follow-up visits

After hospital discharge, routine clinical follow-up is planned in all patients at 1, 6, 12 months, and yearly up to three years. At each visit, the clinical outcomes (death or readmission to hospital for any cause), compliance with medical therapy and smoking cessation, will be assessed. LDL, blood pressure and glycemic targets will be assessed. Validated questionnaires assessing the quality of life (EuroQol-5D, EQ-5D) and physical activity at home (Community Healthy Activities Model Program for Seniors, CHAMPS) will be administered. Physical performance will be assessed in terms of gait speed, handgrip and SPBB. Transthoracic echocardiography will be performed at discharge and during the one-year follow-up visit.

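### The only test named for event-free survival is a log-rank test without covariates; pre-specified adjustment for baseline prognosis would probably add a little power

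*Protocol article*

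**What the plan says.** All places are in the protocol article.

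- **Endpoint** (Study endpoints): "The primary endpoint is the one-year occurrence of CV death or hospital readmission for CV causes". Only the first event counts.
- **Test** (Statistical considerations): Kaplan–Meier curves are to describe freedom from adverse events, and the "difference between groups will be tested with the log-rank test". No covariate, stratified test or regression model is named. The section presents itself as a summary and says that a detailed SAP will follow.
- **Baseline data** (Screening, inclusion visit and randomization): the eCRF holds "inclusion/exclusion criteria, demographics, medical history, CV procedures, exams and treatments, laboratory test results". SPPB is scored again at T1, before allocation.
- **Echocardiography** (Follow-up visits): "Transthoracic echocardiography will be performed at discharge and during the one-year follow-up visit".
- **Randomization strata**: sex, SPPB band (4–6 or 7–9), type of MI and centre. The analysis text does not mention them again.
- **Prognosis** (Introduction): older MI patients are said to have several comorbidities and unrecognized but "prognostically significant risk factors, such as low physical performance".

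**The concern.** In a time-to-event comparison, a strong baseline predictor that is left out pulls the marginal hazard ratio towards 1 relative to the conditional one and usually costs some power. Here the candidate predictors are already collected. Respecting the randomization strata would not use them fully: age and LVEF are not strata, and SPPB is a stratum only as a two-level band.

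The trial is small in events. At the planned size, 152 × 0.25 + 304 × 0.15 = 38 + 45.6, or about 84 primary events, are expected. A few points of power from data already held would be worth having.

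**Working it through.** **1. The plan's own figure.** The sample-size section states "based on alpha = 0.05 and beta = 80%, a total sample size of 435 patients is required"; the 80% is read as power. The risks are p1 = 0.25 (control) and p2 = 0.15 (intervention), with k = 2 intervention patients per control. The usual two-proportion formula with pooled variance is

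n(control) = [z_α √((1 + 1/k) p̄(1 − p̄)) + z_β √(p1(1 − p1) + p2(1 − p2)/k)]² / (p1 − p2)²

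- p̄ = (0.25 + 2 × 0.15)/3 = 0.1833, so the first root is √(1.5 × 0.1497) = 0.474.
- The second root is √(0.1875 + 0.06375) = 0.501.
- One-sided 0.05: (1.645 × 0.474 + 0.842 × 0.501)² / 0.01 = 144.3, so 145 controls and **435** in total, as stated.
- Two-sided 0.05: (1.960 × 0.474 + 0.842 × 0.501)² / 0.01 = 182.4, so 183 controls and 549 in total.

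The article does not state sidedness. At two-sided 0.05, 435 patients give 70.9% power. This is a separate matter, but it explains why the unadjusted powers below sit near 72% and not 80%.

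**2. What adjustment adds.** Event times were simulated as exponential over one year. One normally distributed baseline score acts on the log hazard, and baseline hazards are set so that the marginal risks stay at 25% and 15% (marginal hazard ratio ln 0.85 / ln 0.75 = 0.565). The strength of the score is an assumption.

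Log-rank test against Cox model with the score; 145 vs 290 patients, no loss, two-sided 0.05; 10,000 runs per row (4,000 in the first and last):

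| Concordance index | Log-rank | Adjusted | Gain (points) |
|---|---|---|---|
| about 0.5 (no prognostic value) | 72.0% | 71.5% | −0.5 |
| 0.575 | 71.5% | 71.5% | +0.1 |
| 0.60 | 71.2% | 72.3% | +1.0 |
| 0.63 | 71.7% | 72.8% | +1.2 |
| 0.65 | 71.7% | 74.3% | +2.6 |
| 0.68 | 71.8% | 75.4% | +3.7 |
| 0.70 | 71.9% | 76.9% | +5.1 |
| 0.74 | 73.3% | 83.2% | +9.9 |

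The Monte Carlo standard error of the gain is 0.2 to 0.3 points in the 10,000-run rows. At one-sided 0.05 the gains are similar: about 0, 2.2, 3.2 and 4.6 points at 0.575, 0.65, 0.68 and 0.70.

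Planned size (152 vs 304, 5% loss), indexed by the c-statistic for a one-year event:

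| One-year c | Adjusted for | Unadjusted | Adjusted | Gain (points) |
|---|---|---|---|---|
| 0.59 | score + 4 noise covariates | 72.2% | 73.5% | +1.3 |
| 0.65 | score + 4 noise covariates | 72.4% | 74.4% | +2.0 |
| 0.66 | score only | 71.6% | 74.3% | +2.7 |
| 0.72 | score + 4 noise covariates | 72.8% | 77.2% | +4.4 |
| 0.72 | score only | 72.5% | 77.4% | +4.9 |
| 0.77 | score + 4 noise covariates | 71.5% | 81.8% | +10.3 |
| 0.78 | score only | 71.0% | 80.9% | +9.9 |

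The two scales differ slightly. A score with SD 0.5 on the log hazard has a concordance index of 0.63 and a one-year c of 0.65 to 0.66; SD 1.0 gives 0.74 and 0.77 to 0.78. Allowing for that, the tables agree.

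**3. Reading.** The gain rises steeply with covariate strength and is negligible when the covariates are weak. Four useless covariates in the model do no material harm. With a score of no value at all, the −0.5 point is small and may be simulation error.

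**The case against.** The case against is substantial, and most of it stands.

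- **Validity.** A log-rank test is a valid test of the treatment effect in a randomized trial, and it matches a sample size built on marginal risks. A reader might infer that the planned result would be biased towards no effect. It would not: the marginal and conditional hazard ratios are different quantities, and the planned one is estimated properly.
- **Summary text.** The article never calls the log-rank test unadjusted or the sole primary analysis, and it defers detail to a SAP that is not shown. A reader might infer that the sponsor has ruled adjustment out. The text does not say so, and the SAP may already adjust.
- **Size.** A reader might infer that several points of power are being given up for nothing. No document gives a prognostic strength, and enrolment narrows the spread of the predictors (age 65 or over, SPPB of 4–9 confirmed twice). Adjustment also has costs.
- **Textual support.** The Introduction calls low physical performance prognostic. It does not say this of age or LVEF. LVEF is named only in the abbreviation list of Fig. 1; diabetes and renal function are not named at all.

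What remains is that the one method named for event-free survival uses none of the baseline data, and a better-powered alternative is available from data already planned for collection.

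**Conclusion.** The point holds as an efficiency improvement to settle in the SAP, not as an error in the protocol. The expected gain is about 0 to 1 point of power at a c-statistic of 0.60 or less, about 1 to 3 points near 0.65, and 4 to 5 points near 0.70 to 0.72. About 10 points needs a one-year c of 0.77 to 0.78 (concordance index 0.74), which nothing in the documents supports.

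These figures assume the planned 25% and 15% risks, proportional hazards given the score, and a two-sided 0.05 test. It would also be too strong to treat adjustment as a remedy for the sample size matching only a one-sided test: going from about 71% to 80% would take covariates of that top strength.

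**What to change.** Before any arm-level data are seen, write into the SAP a covariate-adjusted primary analysis truncated at one year, with a short fixed list. An example is age and T1 SPPB score as continuous variables, plus LVEF if it is recorded for all patients, alongside the randomization factors. Choose one form:

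- a covariate-adjusted log-rank test or a standardised one-year risk difference, which keeps the marginal estimand; or
- a Cox model with treatment and the listed covariates, whose hazard ratio is conditional on them.

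Keep the Kaplan–Meier curves and the plain log-rank test as the unadjusted sensitivity analysis. If the SAP already does this, only confirmation is needed.

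The cost is wording, with no new data. Missing baseline values need a simple rule stated in advance. Under the Cox option the reported hazard ratio changes meaning: in the simulations it was 0.562 at a concordance index of 0.575 and 0.538 at 0.70, against a marginal 0.565.
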